#### Process evaluation: MI integrity and MI fidelity

To check whether MI was implemented and delivered as intended, an evaluation of treatment fidelity and treatment integrity is important.

Also given the explicit emphasis in MI as a spirit rather than a technique [93], treatment fidelity and treatment integrity will be measured. Therefore, the MI Treatment Integrity Code (MITI version 3.1) [94] will be used. It has shown to be a cost-effective and reliable tool [95,96], which is also validated to check MI fidelity [94,97]. Feedback during the training and during intervision sessions will be delivered based also on the MITI. Research has also shown that proficiency rating by skilled coders predicted treatment outcome [98-100]. To be able to do so, all pre-treatment sessions are audio taped, and a random sample of 20% of all sessions will be scored by one of the authors ([name]). Twenty per cent out of those will also be scored by another skilled coder (NN) using the abovementioned MITI instrument.

#### Process evaluation in participants and nurses

A process evaluation is needed to evaluate the actual delivery of our pre-treatment intervention, the process evaluation focuses on the level of nurses and patients [101].

1. Patients: Patients will be asked to score their satisfaction with pre-treatment in a set of questions for process evaluation purposes at the end of the pre-treatment intervention (included in the questionnaire of T1). In case of treatment drop-out, a patient is asked to answer the questions regarding satisfaction with the (pre-) treatment directly after the decision to stop, including reasons for drop-out from treatment.

Furthermore, client-centeredness will be assessed by the Client Centred Care Questionnaire (CCCQ). The questionnaire was originally developed for the use in clients receiving homecare [102]. By making some minor revisions, it can also be used in the rehabilitation setting [103]. It has shown good psychometric qualities [102].

2. Nurses: After both pre-treatment sessions, nurses are asked to fill in a short questionnaire. Questions are asked about the steps taken during the intervention, the content of the discussion during the sessions, and the client’s active participation. The questionnaire’s structure is based on the work of Steckler and Linnan [101] and adapted to the specific situation of our study.

### Statistical analysis

The statistical analysis for the effect evaluation, the cost-effectiveness evaluation and cost-utility analysis, and the process evaluation will be described separately. Data will be analyzed using SPSS version 17.

#### Effect evaluation

Baseline data will be analyzed to describe the characteristics of all participants and to check for significant imbalances between the two groups. Possible baseline differences between the intervention group and the control group will be tested by an independent samples *t*-test (normal distribution) or Mann–Whitney U tests (non-normal distribution) in the case of continuous variables. In the case of dichotomous variables, a Chi-square test will be used. In case of imbalances in prognostic factors between both randomized groups, an adjustment for those factors will take place. The number of drop-outs and follow-up losses in both groups will be reported based on descriptive data. Differences in primary and secondary outcome measures between MIP and UC will be analyzed using repeated measurements techniques and multilevel analysis. This approach is chosen because repeated measures within individual subjects are taken. A *P* value <0.05 is considered statistically significant. Data will be analyzed according to the intention-to-treat principle. All outcomes will be assessed at each follow-up moment by taking into account a specific a priori hypothesis. Additionally, per protocol analyses will be performed to assess whether protocol deviations have caused bias.

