### Sample size

The sample size calculation is based upon an estimated difference in change in level of participation between baseline and 6-month follow-up (after completion of the rehabilitation treatment) as assessed by the Utrecht Scale for Evaluation of Rehabilitation-Participation (USER-P) [35,36]. Reproducibility [37], responsiveness [38], and validity [37] of the USER-P are satisfactory. As participation is the important outcome in rehabilitation, we have chosen this as primary outcome. The scale consists of the three aspects of participation represented by the subscales Frequency, Restriction, and Satisfaction. The sum score of each subscale is converted to scores on a scale ranging from 0 to 100. There is no USER-P total score.

Our sample-size calculation is based upon the subscale Satisfaction. This subscale is the most important part of participation as it marks the subjective experience of participation [9]; therefore we have chosen this one.

As at this moment no information is available about the USER-P in a pain population regarding normative values, clinically relevant change, and clinically relevant difference, our study is exploratory of character. In a study by van der Zee (2011) the USER-P is taken in different patient groups at three different points in time [38]. As these groups were part of a cohort study, nothing is known about differences after a specific treatment. We know from other studies that multidisciplinary pain rehabilitation treatment is moderately effective with effect sizes ranging from 0.30 for behavioral outcomes up to 0.40 for functional outcomes [14]. We expect an additional effect for the MIP intervention since systematic reviews of motivational interviewing-based interventions show an effect size ranging from 0.27 up to 0.40 when compared with a weak comparison group [30-32,39]. It has to be said that in those reviews no study in the field of chronic pain or rehabilitation treatment was taken into account. Therefore, our power calculation is based on the following two assumptions:

1. Using an expected mean change of 5 points within UC is expected whereas a difference of additional 5 points (thus at least 10 points in total) within MIP in the USER-P sub scale Satisfaction is considered as clinically relevant. Those numbers are estimates as the clinically relevant difference is not known yet.

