2. Assuming a standard deviation of 10 points in both groups, the standardized effect size, Cohen’s d, is (10–5)/10 = 0.5 indicating a medium additional effect size of the MIP [40].

Assuming power (1-β) of 80%, α = 0.05, two-sided testing, and holding the above mentioned assumptions, would necessitate *n* = 128 participants (*n* = 64 per arm). With an expected total drop-out of 20% (10% drop-out from the study, another 10% drop-out during the usual rehabilitation treatment as our unsystematic registration has shown), *n* = 160 (*n* = 80 per arm) was chosen as the optimal total sample size. Additionally, as the recruitment of 160 participants in the region of South-Limburg/the Netherlands is feasible in a time range of 18 months, we have chosen for this amount of participants.

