### Informed consent, randomization, and blinding

Standard informed consent procedures will be used. After having received informed consent, the participants are randomly assigned to either the experimental intervention condition (MIP) or the control condition (UC). Block randomization with block size of four are used per study site (hospital) to obtain equal numbers in both arms. An independent research assistant will execute the randomization by means of a computerized random number generator resulting in a computer-generated list of random numbers to allocate the participant either to the experimental or the control condition. The consultant in rehabilitation medicine, the rehabilitation team and the participant will all be blind for the result of the allocation to the UC or the MIP but not for participation in the study at all. The research assistant responsible for the logistics of the present study and the participating nurses administering the intervention and control condition are not part of the treatment team and are not blinded for allocation.

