#### Primary outcome

The primary outcome of the effect-evaluation will be the mean difference in change in level of participation of the participants at T4 compared to T0 (baseline).

Participation will be measured by the Utrecht Scale for Evaluation of Rehabilitation-Participation (USER-P) [54]. It consists of 32 items and covers three aspects of participation, namely Frequency, Restriction, and Satisfaction. The subscale Frequency consists of 12 items and assesses vocational activities, and frequency of leisure activities and social activities. Each item is scores from 0 (‘not at all’) up to 5 (‘36 hours or more’/’19 times or more’). The subscale Restriction comprises 10 items assessing experiences in vocational and leisure activities. Items are rated on a four-point Likert scale ranging from 0 (‘not possible at all’) to 3 (‘independent without disability’). The subscale Satisfaction consists of 10 items and rates satisfaction regarding participation in daily life issues such as work and social relations. Items are rated on a five-point Likert scale ranging from 0 (‘not satisfied at all’) to 4 (‘very satisfied’). Higher scores reflect more social participation (each higher frequency, less restrictions, higher satisfaction). The psychometric qualities validity and reproducibility are satisfactory [36,55].

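### Covariate adjustment depends on baseline significance tests, so baseline USER-P would enter only by chance and hospital practically never; both should be fixed in the primary model in advance

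*Protocol article*

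**What the plan says.** The Effect evaluation section examines baseline data "to check for significant imbalances between the two groups", using t, Mann-Whitney or chi-square tests according to the type of variable. The rule that follows is conditional: "In case of imbalances in prognostic factors between both randomized groups, an adjustment for those factors will take place". Outcomes are then to be "analyzed using repeated measurements techniques and multilevel analysis"; the section does not say how the baseline value enters or what the levels are.

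The Primary outcome section defines the target: "The primary outcome of the effect-evaluation will be the mean difference in change in level of participation of the participants at T4 compared to T0". The Sample size section works on the same scale, with a mean change of 5 points under usual care and 10 under the intervention on the Satisfaction subscale, "Assuming a standard deviation of 10 points in both groups". The section on randomization says that allocation is blocked within each hospital in blocks of four, and the Recruitment section names two hospitals. No section names baseline USER-P or hospital as a covariate to be included regardless of the data.

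**The concern.** Allocation is by computer-generated random list, so any baseline difference between the arms is chance. A significance test of such a difference tests a hypothesis already known to be true, and its result says nothing about whether the variable predicts the outcome. A covariate improves precision through its correlation with the outcome, however well balanced it happens to be. A rule triggered by imbalance therefore settles the model only after the data are seen, and on the wrong criterion.

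Two variables can be named beforehand: the baseline value of the outcome, and the hospital within which patients were randomised. The stated rule brings in the first only when chance produces an imbalance. It practically never brings in the second, because the blocking keeps it balanced. At stake is precision from data already collected, in a trial whose 5-point difference the article itself calls an estimate and whose SD is assumed.

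**Working it through.** **Inputs from the article.** Difference in mean change 10 − 5 = 5 points; SD 10; two-sided alpha 0.05; power 80%; drop-out 20%; blocks of four within each of two hospitals.

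**Assumed, because the article gives no figure.** The T0-T4 correlation of USER-P Satisfaction, ρ, from 0.3 to 0.8; the between-hospital share of variance, v, from 1 to 10%.

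**1. The plan's own figure.** d = 5/10 = 0.5. The exact two-sample t-test needs 63.8, so 64 per arm (128 in all), with power 80.1%. For drop-out, 128/0.8 = 160. The stated 128 and 160 are reproduced, for an unadjusted comparison of change.

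**2. Always adjusting for baseline, with SD 10 as the SD of change.** The variance ratio of the adjusted to the plain change-score analysis is (1 − ρ²)/[2(1 − ρ)] = (1 + ρ)/2, so the residual SD is 10·√((1 + ρ)/2).

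| ρ (assumed) | (1 + ρ)/2 | Residual SD | d = 5/SD | Power at 64 per arm | n per arm for 80% |
|---|---|---|---|---|---|
| plain change score | 1 | 10 | 0.50 | 80.1% | 64 |
| 0.3 | 0.65 | 8.06 | 0.62 | 93.6% | 42 |
| 0.5 | 0.75 | 8.66 | 0.58 | 90.0% | 49 |
| 0.7 | 0.85 | 9.22 | 0.54 | 86.1% | 55 |
| 0.8 | 0.90 | 9.49 | 0.53 | 84.1% | 58 |

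**3. If SD 10 is the SD of the score instead.** The SD of change is then 10·√(2(1 − ρ)) and the adjusted residual SD is 10·√(1 − ρ²). Power for change score against adjusted is 66% against 84% at ρ = 0.3, 80% against 90% at 0.5, and 95% against 98% at 0.7. The adjusted analysis is better in each case.

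**4. The conditional rule.** A 5% test flags baseline USER-P in about one randomised trial in twenty. In 10,000 simulated trials per setting (64 per arm, SD of change 10, baseline the only candidate covariate):

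| ρ | Change score | Always adjust | Adjust only if baseline test is significant | Type I error of the conditional rule |
|---|---|---|---|---|
| 0.5 | 80.1% | 89.3% | 81.1% | 4.4% |
| 0.7 | 80.7% | 85.8% | 81.3% | 4.6% |

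The conditional rule recovers almost none of the gain.

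**5. Hospital.** Blocks of four limit the arm difference within a hospital to two patients. As an illustration, take hospitals of 78 and 82 patients, split 40/38 and 40/42. The chi-square statistic is 160 × (40×42 − 38×40)²/(78×82×80×80) = 0.10, against a 5% critical value of 3.84. An imbalance test will practically never select hospital. Including it anyway gives a residual SD of 10·√(1 − v), and power at 64 per arm of 80.5%, 82.1% and 84.1% for v = 1, 5 and 10%.

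**The case against.** The strongest reply is that this is a condensed article and that model terms are commonly left to the analysis plan. A reader might infer that the primary analysis adjusts for neither baseline USER-P nor hospital. The documents do not say that. A repeated-measures model with a common baseline mean, or with baseline as a covariate, has the efficiency of the adjusted analysis, and a multilevel model may include hospital. Defining the outcome as change does not rule out baseline adjustment either. If baseline is one of the repeated outcomes with free arm means at T0, the T4 contrast does reduce to unadjusted change, but the article does not choose that model. So the power comparison is conditional on a plain change-score comparator. The stated adjustment rule remains open to criticism, because it is written out and is not a gap.

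Other stronger readings also fail:

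- **Underpowered, or false positives inflated.** The planned 80% is met without adjustment, and the simulated type I error of the conditional rule is slightly below 5%.
- **A 54% chance that the model changes.** Counting the 15 baseline items in the Demographic and medical variables section, 1 − 0.95¹⁵ = 0.54. That is the chance that some test is flagged if the items are independent. Adjustment is restricted to prognostic factors, and several items are likely to be correlated, so it is not the chance that the primary model changes. For the same reason, selection is not by p-value alone, although imbalance remains the trigger.
- **Patients with a missed visit deleted by classical repeated-measures ANOVA.** The article does not choose that method, and pairing the phrase with multilevel analysis and intention-to-treat points away from it.

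**Conclusion.** The point holds as a criticism of the stated covariate rule. The rule makes adjustment depend on chance imbalance and guarantees a place to neither of the two variables that can be justified before any data are seen. No bias or loss of the planned power is shown. The forgone gain is about 4 to 14 percentage points of power at 64 per arm, equivalent to needing 10 to 35% fewer patients for 80%. This rests on an assumed correlation between 0.8 and 0.3, on the SD of 10 being that of change, and on a plain change-score comparator. The gain from hospital is small unless the two sites differ markedly; the reason to include it is that the analysis should reflect the stratified randomisation. The change is worth making because it is free, not because the trial fails without it.

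**What to change.** Delete the baseline significance tests and the rule that adjusts when an imbalance appears, and present baseline characteristics descriptively by arm. State that the mixed (multilevel) model for the T4 arm contrast includes, as fixed covariates whatever the observed imbalance, the baseline value of the USER-P score being analysed and hospital. Name any further covariate in advance, on prognostic grounds.

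The cost is wording in the protocol or analysis plan. USER-P is already measured at T0 and the hospital of each patient is known, so no new data are needed. The article describes recruitment as still under way, so the change could be made before the outcome data are complete.

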### Moderation analysis

As secondary analyses, the working mechanisms of MI are investigated. For testing moderation, an interaction term of the potential moderator is constructed and analyzed by linear regression.

### Economic evaluation

In the economic evaluation, cost and effects of usual care and MIP will be calculated and compared. Therefore, the cost per patient year (=participant year) will be calculated. This means that all observed costs will be extrapolated to a 1-year period.

The analysis will include those persons for whom at least two of the three follow-up measurements (cost diaries) are available.

For the cost-effectiveness analysis (CEA) the cost-effectiveness ratio will be stated in terms of costs per improvement on participation (as assessed with the USER-P).

For the cost-utility analysis (CUA) the cost-utility ration will be stated based on the cost per (Quality Adjusted Life Year) QALY gained.

Bootstrap (5,000 times) re-sampling techniques will be used to test for differences and uncertainty in costs and effects between the MIP and the UC intervention.

The bootstrapped cost-effectiveness and cost-utility ratios will be subsequently plotted in a cost-effectiveness and cost-utility plane. The results of this study will also be depicted in cost-effectiveness acceptability curves (CEACs) [104].

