**Methods/design:**

Study design: A parallel randomized controlled trial including two interventions: a motivational interviewing pre-pain rehabilitation intervention (MIP) and a usual care (UC) control arm. Follow-up will be 6 months after completion of rehabilitation treatment.

Study population: One hundred and sixty (*n* = 80 per arm) patients with chronic non-specific musculoskeletal pain visiting an outpatient rehabilitation department, who are eligible to participate in an outpatient cognitive behavioral pain rehabilitation program.

Intervention: MIP consists of two sessions to prepare and motivate the patient for pain rehabilitation treatment and its bio psychosocial approach. UC consists of information and education about the etiology and the general rehabilitation approach of chronic pain. Both the MIP and UC contain two sessions of 45 to 60 minutes each.

Objective: The aim of the current study is to evaluate the effectiveness of MIP compared to UC in terms of an increase in the long-term level of societal participation and decrease of drop-out during rehabilitation treatment.

Main study endpoints: Primary outcome is the change in level of participation (according to the ICF-definition: ‘involvement in a life situation’) 6 months after completion of rehabilitation treatment. Secondary outcomes are adherence and treatment drop-out, disability, pain intensity, self-reported main complaints, (pain-specific) self-efficacy, motivation, and quality of life. Costs are calculated including the costs of the pre-treatment intervention, productivity losses, and healthcare utilization. Potential moderators and active ingredients of MI are explored. For the process evaluation, parameters such as MI fidelity, feasibility, and experiences are explored.

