#### Current care in pain rehabilitation

In the current pain rehabilitation treatment in the Netherlands [41] roughly four phases can be identified. The specific content of the phase can differ per center.

The four phases are:

1. Screening: In this phase, a patient’s eligibility and readiness for pain rehabilitation is assessed. Also information is provided by either a consultant in rehabilitation medicine or a nurse practitioner. In most centers for this purpose use existing educational material, such as ‘De pijn de baas’ (‘Mastering pain’) [42] or ‘Explain Pain’ [43] (WPN, 2012, internal document) are used as information tools for this purpose. In most places, information is given before the definite start of the treatment.

2. Observation: A patient’s pre-treatment situation and motivation is assessed, and the most suitable type of treatment is selected. In some centers, this phase takes two or three sessions in 2 to 4 weeks. Often this is accompanied by the use of self-report questionnaires.

3. Rehabilitation treatment: The multidisciplinary pain rehabilitation treatment lasts for around 3 months with an intensity of 2 or 3 days a week on average. Depending on the patients’ limitations and underlying problems, different treatment approaches such as graded activity and/or graded exposure are used in combination with other psychosocial and physical interventions.

4. Aftercare and post rehabilitation treatment assessment: Booster sessions, tailored to patients’ needs, are given for relapse prevention and long-term facilitation of applying learned skills to maintain and further improve participation. The moment of the assessment is around 6, 12, 24, to 52 weeks post-treatment. These follow-up appointments are mostly accompanied by completion of self-report questionnaires for treatment evaluation. It has to be said that this is not routine care in all Dutch rehabilitation centers.

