#### PREPARE conditions

The PREPARE intervention focuses on phase one. This is also the period during which patients are waiting before they can start their actual treatment (observation and rehabilitation treatment). During the study, patients will receive either the new MI-based intervention or care as usual. In order to standardize treatment options, both arms (MIP as well as UC) will include two sessions with identical contact time. In order to prevent contamination of treatment, each treatment condition will be delivered by different nurses. Figure 1 illustrates the situation during the PREPARE study.

1. Usual care (UC)

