### Data collection

For the (cost-) effectiveness evaluation, measurements will be carried out before the first MIP/UC pre-treatment sessions (T0), after the MIP/UC (T1 = post pre-treatment), after the regular multidisciplinary pre-rehabilitation assessment (before starting rehabilitation), at the start of the pain rehabilitation treatment (T2), after treatment completion (T3), and at 6-month follow-up (T4). Study assessments at T0, T2, and T3 will be integrated in current care clinical assessment battery pre-rehabilitation and post rehabilitation (see also Figure 1 (flow-chart) and Table 2). Cost measurements will be carried out at three points: T0, T2, and T4. Information on drop-out from and adherence to the (pre-) rehabilitation treatment, start and end date of the treatment, and no show are derived from the administrative patient registry.

**Table 2 T2:** Outcome measures, abbreviation instrument, and assessment moments PREPARE study

		**Baseline**	**Two sessions**	**After pre-treatment**	**Start pain rehab treatment**	**Finish pain rehab treatment**	**6 months after T3**
	**Abbr.**	**T0**^**a**^		**T1**	**T2**^**a**^	**T3**^**a**^	**T4**

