#### Cost-effectiveness and cost-utility

To evaluate the economic effects of MIP and UC, relevant cost categories of resource use and volumes of these categories will be measured. Finally, volumes are multiplied by the corresponding costs.

The direct (non-)healthcare costs will be assessed with the Trimbos/iMTA questionnaire for Costs associated with Psychiatric Illness (Tic-P) [67]. This self-reporting questionnaire consists of 15 items and assesses healthcare use in a recall period of 3 months.

Productivity losses are assessed by the Short Form Health and Labor Questionnaire (SF-HLQ) [68]. The SF-HLQ measures the extent of production losses of paid and unpaid work in four modules: absence from work, reduced productivity at paid work, unpaid labor production, and impediments to paid and unpaid labor. It consists of 11 items.

For the cost valuation, standardized cost prices will be used from the Dutch manual for cost analysis in healthcare research [69]. Where no standard cost prices are available, real costs or tariffs will be used to estimate costs. Productivity losses will be calculated based on the friction costs method. Cost prices will be presented in Euros and the baseline year is 2012, or otherwise discounted. The discounting rate of costs is 4%, and 1.5% for effects [70]. To analyze differences in costs, costs per patient-year will be calculated.

For the cost-effectiveness analysis (CEA), costs will be weighted against the primary outcome measure participation. The measure is described above.

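### The rule that extrapolates all observed costs to one year exempts no one-off care, so the pre-treatment sessions and other care given once are rescaled as if they recurred

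*Protocol article*

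**What the plan says.** The Economic evaluation section compares the arms on cost per patient-year and defines it: "This means that all observed costs will be extrapolated to a 1-year period". The section on cost-effectiveness and cost-utility uses the same metric: "To analyze differences in costs, costs per patient-year will be calculated". The Abstract lists what enters the total: "Costs are calculated including the costs of the pre-treatment intervention, productivity losses, and healthcare utilization". No section separates one-off from recurring costs, and none states the period over which observed costs are divided before scaling.

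On data capture, the Data collection section says "Cost measurements will be carried out at three points: T0, T2, and T4", and the healthcare cost questionnaire "assesses healthcare use in a recall period of 3 months". Inclusion in the economic analysis requires two of three measurements: "The analysis will include those persons for whom at least two of the three follow-up measurements (cost diaries) are available".

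On the care itself, the section on the PREPARE conditions says that "both arms (MIP as well as UC) will include two sessions with identical contact time". The section on current care describes an observation phase of two or three sessions in some centres, and then the programme: "The multidisciplinary pain rehabilitation treatment lasts for around 3 months with an intensity of 2 or 3 days a week on average". Each of these is given once per patient.

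**The concern.** Scaling an observed cost to a year makes sense for a cost that accrues at a roughly steady rate, such as visits to a general practitioner. It does not make sense for a cost incurred once. Two sessions remain two sessions whether the patient is followed for nine months or fifteen. Under the rule as written, their cost is multiplied by whatever factor brings the observed period to a year.

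At stake are the absolute cost per patient in each arm and, where one-off costs differ between arms, the incremental cost in the numerator of both ratios. The effect in the cost-effectiveness analysis is the change in USER-P from T0 to T4, which the article does not rescale, so a rescaled cost difference passes straight into that ratio.

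**Working it through.** The article states no annualisation factor and no cost figure, so there is nothing of its own to reproduce. The check derives the factor under each denominator that fits the text.

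**Inputs from the article.** Two pre-treatment sessions per arm; recall of 3 months; cost measurements at T0, T2 and T4; at least two of three required; rehabilitation lasting 10 to 16 weeks at 2 or 3 days a week; T4 six months (26 weeks) after T3. 
**Input assumed.** T0-T2 interval of 4 to 26 weeks. The article says only that the wait between T1 and T2 varies.

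**Denominator 1: recall months covered (assumption).** Factor = 12 / (3 × number of questionnaires).
- Three questionnaires: 12/9 = 1.33, so two sessions are charged as 2 × 1.33 = 2.7.
- Two questionnaires: 12/6 = 2.0, so two sessions are charged as 2 × 2.0 = 4.

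The 1.33 figure counts the T0 recall window, which lies wholly before the first session.

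**Denominator 2: elapsed time T0 to T4 (assumption).** Factor = 52 / (T0-T2 weeks + rehabilitation weeks + 26).
- Shortest: 52 / (4 + 10 + 26) = 52/40 = 1.30.
- Longest: 52 / (26 + 16 + 26) = 52/68 = 0.76.

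The factor is 1 only when follow-up happens to last exactly 52 weeks.

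**Is the rehabilitation programme in the questionnaires?** T2 is taken at its start. T4 is six months after its end, and a 3-month recall at T4 reaches back only to about three months after T3. The stretch after T2 that no recall window covers is 10 + 26 − 13 = 23 weeks to 16 + 26 − 13 = 29 weeks, and it contains the whole programme. Programme days are therefore rescaled only if they are costed from another source, such as the patient registry.

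**Effect on the difference between arms.** Let D be the true difference in one-off cost. It becomes 1.33D or 2.0D under denominator 1, and between 1.30D and 0.76D under denominator 2. If D = 0, each arm's session cost is still misstated, but the average difference stays at zero unless the factor itself differs by arm.

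**Illustration with assumed costs** of 100 one-off and 300 recurring per 3 months, under denominator 1:
- Blanket rule, two questionnaires: 2.0 × (100 + 600) = 1,400.
- Blanket rule, three questionnaires: 1.33 × (100 + 900) = 1,333.
- One-off cost counted once: 100 + 4 × 300 = 1,300 in both cases.

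**The case against.** The strongest reply is that this is a condensed article. The phrase about observed costs stands beside a mention of cost diaries, so it may mean only diary-reported costs, with the intervention cost added separately in a fuller economic plan. That is possible, and it would remove much of the problem. However, the article states a rule covering all observed costs and elsewhere puts the intervention in the total. The rule as printed gives the wrong result for one-off items, which is different from leaving a detail out. Observation visits precede T2 and could also be reported in the T2 questionnaire, so the diary reading would not exempt them.

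A second reply is that session cost cancels because contact time is identical. This largely stands. What does not cancel is any one-off cost that differs by arm. The Nurses section gives the MIP nurses expert training and regular supervision, against a 3-hour refresher and one or two meetings a year for the UC nurses. Hypothesis 1b expects less drop-out and higher adherence under MIP. Neither training nor programme days are stated to be costed, so both routes are conditional.

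A reader might infer more than the document supports:
- That the factor depends on how many questionnaires come back. The two-of-three rule is an inclusion criterion. No denominator is stated, and elapsed time fits the text equally well.
- That one-off care is always overcharged. Under elapsed time the factor can be below 1.
- That better treatment retention under MIP changes the factor. Staying in rehabilitation and returning a cost questionnaire are different things, and the article does not link them.

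**Conclusion.** The point holds as a defect in a stated rule. Care given once is rescaled as if it were a rate, and nothing in the article exempts it. The factor is 1.33 or 2.0 if the denominator is recall months, and about 1.30 down to 0.76 if it is elapsed time with an assumed T0-T2 interval of 4 to 26 weeks. The direction is therefore not fixed, and misstated is the right word rather than overstated.

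The absolute cost per patient is affected in both arms. The cost difference is affected only through one-off costs that differ by arm: MIP training and supervision if costed, and rehabilitation attendance if costed from the registry. The article gives no unit costs, so the size in euros cannot be derived. A general claim that both ratios are materially biased is not supported. The primary effectiveness analysis is untouched.

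**What to change.** Replace the blanket rule with a split:
- Enter one-off items once, at the volume actually delivered. These are the MIP and UC sessions, with training and supervision if costed, the observation visits, and the rehabilitation sessions if costed.
- Annualise only the recurring costs from the questionnaires, using a stated denominator that covers time after T0.
- Add the two parts, and remove from the questionnaire part any one-off item already counted.

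State whether training, supervision and programme days are costed. Also reconcile the mention of three follow-up cost measurements with the schedule, in which one of the three is the baseline at T0.

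The cost is a few sentences in the economic analysis and a small programming change. No new patient data are needed for session volumes, because the Data collection section already takes adherence to the pre-treatment and rehabilitation from the administrative patient registry.
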